## Abstract

**Background:**

Sustained, widespread availability of evidence-based practices (EBPs) is essential to address the public health and societal impacts of adolescent substance use disorders (SUD). There remains a particularly significant need to identify effective financing strategies, which secure and direct financial resources to support the costs associated with EBP implementation and sustainment. This protocol describes a new project comparing two types of U.S. federal grant mechanisms (i.e., a type of financing strategy), which supported the implementation of the Adolescent Community Reinforcement Approach (A-CRA) EBP for SUD, through either organization-focused or state-focused granting of funds. The Exploration-Preparation-Implementation-Sustainment (EPIS) framework will guide our study aims, hypotheses, and selection of measures.

**Method:**

We will employ a longitudinal, mixed-method (i.e., web surveys, semi-structured interviews, document review, focus groups, administrative data), quasi-experimental design to compare the grant types’ outcomes and examine theoretically informed mediators and moderators. Aim 1 will examine the proportion of eligible clinicians certified in A-CRA with adequate fidelity levels (i.e., penetration outcomes) at the end of grant funding. Aim 2 will examine the sustainment of A-CRA up to 5 years post-funding, using a 10-element composite measure of treatment delivery and supervision activities. We will integrate the new data collected from state-focused grant recipients (~85 organizations in 19 states) with previously collected data from organization-focused grant recipients (Hunter et al., Implement Sci 9:104, 2014) (82 organizations in 26 states) for analysis. We will also use sensitivity analyses to characterize the effects of observed and unobserved secular trends in our quasi-experimental design. Finally, aim 3 will use comparative case study methods (integrating diverse quantitative and qualitative measures) to identify and disseminate policy implications about the roles of state- and organization-focused federal grants in efforts to promote adolescent SUD EBP implementation and sustainment.

**Discussion:**

The proposed research will have direct, practical implications for behavioral health administrators, policymakers, implementation experts, and the public. It will offer new knowledge that can directly inform financing strategies to support large-scale, sustained EBP delivery in behavioral health—while advancing implementation science through the use of novel methods to study financing strategies and sustainment.

**Supplementary Information:**

The online version contains supplementary material available at 10.1186/s43058-022-00298-y.

Contributions to the literature
The project will advance understanding of effective financing strategies to support the implementation and sustainment of evidence-based practices for the treatment of adolescent substance use disorders.This project will generate new knowledge about penetration and sustainment outcomes, and mechanisms (i.e., mediators and moderators), for two types of U.S. federal grants (state-focused vs. organization-focused) designed to promote evidence-based practice implementation.This study will provide an example of using a quasi-experimental, mixed-method design and sensitivity analyses to maximize confidence in study conclusions and to identify generalizable conclusions about financing evidence-based practices for policy making.

## Background

In 2020, 1.6 million 12–17-year-olds (6.3% of adolescents) in the USA met the criteria for substance use disorders (SUD)—yet less than one in nine received treatment [1]. Providing high-quality treatment to these youth could help mitigate the adverse consequences of SUDs, including accidents, disease, violence, and criminality, which often last into adulthood [2, 3] and have estimated annual costs of $740 billion [2, 3]. To reduce the public health and societal impacts of adolescent SUD, behavioral health service systems must increase the availability of evidence-based practices (EBPs) for SUD [4–8]. Closing the current research-practice gap will require a better understanding of various strategies that support EBP implementation, defined as the practice of EBPs in everyday service settings [9–12].

The most recent systematic review [7] found that well-established EBPs for adolescent SUDs share several features, including delivery in community settings and a developmentally tailored approach that addresses youth, family, and peer influences. One such EBP is the Adolescent Community Reinforcement Approach (A-CRA [13]), a 12–14-week behavioral treatment for adolescents and young adults that seeks to replace environmental factors supporting substance use with alternative activities and behaviors. A-CRA improved substance use, mental health, and social outcomes in four randomized clinical trials [7], and implementing A-CRA with adequate fidelity predicts comparable clinical outcomes in community settings [14–20]. This project focuses on A-CRA as an exemplar EBP for adolescent SUD that has been widely implemented with a common, yet poorly researched, implementation financing strategy: federal grants.

### A-CRA implementation and sustainment in SUD services

Implementation of EBPs like A-CRA is best understood as a complex, long-term process that requires specific knowledge, skills, and resources—resulting in considerable costs to implementing organizations [10–12, 21, 22]. Public service organizations, including SUD treatment providers, must navigate multilevel contextual influences across Exploration, Preparation, Implementation, and Sustainment phases (as outlined in the EPIS framework [23, 24]) to successfully use an EBP. Various implementation strategies help providers and organizations navigate these phases [25–27]; strategies for A-CRA implementation have largely focused on individual clinicians and supervisors, including didactic training, technology-assisted consultation, and certification in the competent use of model procedures. Individual-focused strategies are important, but rarely sufficient to achieve large-scale penetration, as measured by the proportion of potential providers in a service system using an EBP [28]—let alone sustainment, or continued use of that EBP after initial support for implementation ends [29–31]. Indeed, previous research found that clinicians generally had positive perceptions of A-CRA, but about half discontinued its use due to intra- and extra-organizational factors such as limited leadership support or unstable funding [32–34].

Additional strategies are needed to support A-CRA penetration and sustainment, both key implementation outcomes [23, 24, 28], given that the public health impact remains limited without both widespread *and* long-term EBP use [35]. In particular, financing and budget considerations are essential, but behavioral health administrators must often make decisions about financing EBPs without research-based guidance [8]. Recent research identified financing strategies [36] that help organizations secure and direct financial resources to support implementation and sustainment; examples include increased reimbursement [37], grant or contract funding [38], and earmarked taxes [39]. All strategies involve government or philanthropic funders, and most provide time-limited funding to promote the success of initial implementation [40–46]. Unfortunately, little is known about how financing strategies can be optimized to promote SUD EBP penetration and sustainment [36].

### Current project

Federal initiatives that support EBP implementation offer unique opportunities to identify and more fully understand the impact of financing strategies on a large scale [6, 47]. In one of the largest investments in EBP implementation to date, SAMHSA’s Center for Substance Abuse Treatment has offered two types of discretionary grants to promote A-CRA implementation: “organization-focused” grants directly to treatment organizations and “state-focused” grants to state substance use service agencies. With state-focused grants, SAMHSA sought to spread A-CRA to a great number of providers within awardee states and create state-level infrastructure to support A-CRA sustainment. These two grant initiatives provide a natural experiment to compare penetration and sustainment outcomes between different financing strategies in cases where the EBP (A-CRA) and other implementation strategies were the same.

The current project will use a longitudinal, mixed-method approach to gather data from state-focused grant recipients, aligned with previous work [48] that described implementation and sustainment among organization-focused grant recipients. We will integrate data from both projects to compare A-CRA outcomes between state-focused versus organization-focused grants. Figure 1 depicts the proposed natural experiment, illustrating how each grant type is thought to impact outcomes in the implementation and sustainment phases. Following the EPIS framework [23, 24], all grants targeted “inner” (intra-organizational) context factors and state-focused grants also targeted the “outer” (extra-organizational) context.

**Fig. 1 Fig1:**
[figure not shown]
Pathways of proposed grant type effects on A-CRA implementation and sustainment outcomes. A-CRA = Adolescent Community Reinforcement Approach. SUD = substance use disorder. Predicted inner- and outer-context moderators and mediators of outcomes are shown by dotted arrows and round rectangles; mediators are distinguished by the additional dotted arrows showing their being affected by state-focused grants

Our aims are to compare state-focused versus organization-focused SAMHSA grants on A-CRA (1) penetration, defined as rates of certification among eligible clinicians, and (2) sustainment, measured over a 5-year post-grant period. We hypothesize that state-focused grants will have higher rates of penetration and sustainment and that these effects will be moderated by inner- and outer-context factors that are associated with implementation success [49, 50]. We will also (3) identify policy implications for financing the implementation and sustainment of adolescent SUD EBPs through federal grants. Importantly, we do not propose to isolate the causal impact of grant type on outcomes; such conclusions are not possible without a fully randomized design and are unnecessary for answering our research questions. Rather, to increase our policy impact, researchers need to offer a wide range of rigorous, externally valid forms of evidence that policymakers can use [51–54].

## Method

### Research design

Aims 1 and 2 use a longitudinal, natural experiment design to compare A-CRA penetration and sustainment for state-focused grants (new data collection) versus organization-focused grants (collected previously [48]). Given that this is a natural experiment wherein we did not assign participants to grant types, we will conduct a sensitivity analysis that characterizes the influence of observed and unobserved secular trends on our estimates of grant type effects. Aim 3 will use a comparative case study design [55, 56] to identify policy implications for federal SUD service grants. Across aims, qualitative and quantitative data will be collected concurrently within a mixed-method approach [57].

In this protocol, we followed the Standards for Reporting Implementation Studies [58] (StaRI; see Additional file 1) for describing our project. All described procedures were reviewed and approved by the RAND Corporation IRB (Protocol #2020-N0887).

### Project context

As noted earlier, SAMHSA has used both organization-focused and state-focused discretionary grant strategies to fund EBP implementation (including A-CRA) for adolescent SUD. All grants were administered by SAMHSA’s Center for Substance Abuse Treatment [59], whose primary role was to provide funding, oversight, and national leadership to grantee organizations and states/territories/tribal entities (hereafter, “states”). SAMHSA funded (i) four cohorts of organization-focused grantees, awarded 2006–2010, across 26 states followed by (ii) four cohorts of state-focused grantees, awarded 2012–2017, across 22 states. Eight states had recipients of both grant mechanisms, so overall, 40 states were represented across cohorts.

In both initiatives, SAMHSA partnered with Chestnut Health Systems (CHS; an organization that conducts A-CRA training and research) to provide training and certification for A-CRA clinicians and supervisors. CHS provided a standardized, 2.5-day training for all organization-focused grantees and most clinicians in state-focused grantees’ states—although some received training from certified A-CRA supervisors. In every case, CHS still oversaw A-CRA clinician and supervisor certification. Certification activities required each trainee to demonstrate competency in delivering A-CRA treatment and/or supervision procedures, depending on their role. Specifically, clinicians and supervisors participated in twice monthly, group-format coaching calls with CHS expert consultants; they also submitted audio-recorded A-CRA therapy or supervision sessions, respectively, and their consultant provided numeric ratings and written feedback [60–62]. Typically, the certification process lasted from 6 months to a year.

Next, we describe the two grant types in more detail. We follow recommendations for specifying implementation strategies in terms of actors, actions, action targets, temporality, dose, outcomes, and justification [27, 36].

#### Organization-focused grants

SAMHSA awarded these grants directly to treatment organizations. Grantees received ~$900,000 across a 3-year period to support A-CRA implementation. These grants targeted the EPIS inner context by paying for clinicians delivering A-CRA, supervisors providing A-CRA supervision, and related activities such as evaluation (see https://externallinks.samhsa.gov/grants/2009/ti_09_002.dhtml to view a representative request for proposals). Our prior work showed that grantees generally had initial success in implementing A-CRA with fidelity and reducing youth substance use, but many did not sustain A-CRA post-funding [32–34].

#### State-focused grants

SAMHSA awarded these grants to state agencies that administer publicly funded SUD services. These were ~$3–4 million, 3- to 4-year awards (sometimes extended to 6 years) that could support the implementation of several EBPs; most funded states selected A-CRA. The grants targeted EPIS outer context factors [4, 43, 63]—one third of the grant funds paid for states to develop EBP-focused infrastructure like funding, training, developing policies, and promoting treatment organizations’ capacity to deliver youth SUD treatment. State agencies proposed up to six “dissemination site” organizations that implemented A-CRA first; those sites received funds similar in amount and purpose to those provided to organization-focused grantees, thus still addressing inner context factors. See https://www.samhsa.gov/grants/grant-announcements/ti-17-002 to view a representative request for proposals. The outcomes of state-focused grants have not been evaluated.

### Participants

Participants will include state SUD agency administrators, clinicians, and supervisors from treatment organizations that implemented A-CRA (in both state-focused and organization-focused grants), and other state and federal agency administrators whose work is relevant to youth SUD treatment.

#### State SUD service agencies

We will recruit state agency administrators from each state that received a state-focused grant. To be eligible, administrators must be currently or recently employed in a leadership position that involved administration of a SAMHSA state-focused grant from the past 5 years; we will seek to interview one administrator per state, but will permit group interviews when appropriate. Three states’ grants ended more than 5 years ago, so SUD service agency administrators from 19 states are eligible for participation.

#### Treatment organizations

In our previous project, we collected semi-structured interview and survey data from 169 clinicians and supervisors at 78 treatment organizations (across 27 states) that received SAMHSA organization-focused grants [33, 34]. The current project involves collecting similar data from treatment organizations that received support from their state agency to implement A-CRA as part of a state-focused grant, including the dissemination sites and any other organizations that implemented A-CRA. To be included in the current project, organizations must be located in a state where less than 5 years have passed since their state-focused grant ended.

Given the larger scope of state-focused grants, we will not collect data from every treatment organization involved (across the 19 eligible states, CHS records indicate that staff from 282 organizations received A-CRA training). Instead, we used a three-step sampling procedure to select up to five organizations per state from which data will be collected; this approach kept data collection feasible and ensured that organizations from highly successful states were not overrepresented. First, we identified five organizations (in four states) that received training through a state-focused grant while their organization-focused grant was still active, and excluded them due to the extent of confounding. Second, we selected up to three dissemination sites to ensure we included some organizations targeted directly by state-focused grants without overrepresenting the organizations most likely to implement A-CRA successfully; we randomly selected three dissemination sites if a state had more. Third, we randomly selected from the remaining treatment organizations in each state until we reached a maximum of five per state. These procedures selected 91 organizations (*M* = 4.78 per state) from which we will recruit. Chi-squared tests using CHS administrative data indicated that clinicians and supervisors from the selected organizations were no more or less likely to be A-CRA certified (*χ*^2^_(1)_ = 3.416, *p* = .065) or to have left the organization (χ^2^_(1)_ = 2.480, *p* = .115) than those not selected.

Individuals currently or recently employed as a clinician or clinical supervisor responsible for adolescent SUD treatment will be eligible to participate (with a preference for individuals knowledgeable about A-CRA implementation). We kept eligibility criteria for clinicians and supervisors consistent with the previous organization-focused sample [34], which will allow us to combine the data for analyses. The previous sample [34] had an average of 2.17 participants per organization (41% clinicians, 59% supervisors), and we will aim for a similar breakdown of participants. A maximum of 197 clinician and supervisor participants may be included in the state-focused grant sample. Also, in cases where an organization no longer operates adolescent SUD treatment services, we may instead collect data from program directors or other administrative staff with knowledge about the organization’s SUD treatment services.

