### Data sources and collection procedures

We will collect four waves of quantitative and qualitative data from state-focused grantees, to be combined with administrative records from CHS and previously collected data from organization-focused grantees. Table 1 details the planned data collection schedule. In each wave, we will collect data (semi-structured interviews, surveys, document review) from state agency representatives and clinicians/supervisors. Treatment organizations that report no longer delivering A-CRA will complete the ongoing wave of data collection, but will only participate in subsequent waves if they begin delivering A-CRA again and thus have new information to share (we will verify at the beginning of each wave). Focus groups with state and federal agency administrators will take place in the final year and so are not included in Table 1.

**Table 1 Tab1:** Waves of planned data collection for state-focused grant cohorts

Grant cohort (years)	Target # of organizations	Expected # of respondents	Data collection waves: years since funding ended			
			Wave 1 (2021–2022)	Wave 2 (2022–2023)	Wave 3 (2023–2024)	Wave 4 (2024–2025)
(1) 2013–2017	7 states 37 organizations	7 state agency administrators 33 clinicians 47 supervisors	4 years Post-funding	^a^5 years post-funding	*NA*	*NA*
(2) 2012–2018	7 states 33 organizations	7 state agency administrators 29 clinicians 42 supervisors	3 years Post-funding	^a^4 years post-funding	^a^5 years Post-funding	*NA*
(3) 2017–2021	5 states 21 organizations	5 state agency administrators 19 clinicians 27 supervisors	0 years Post-funding	^a^1 year post-funding	^a^2 years Post-funding	^a^3 years Post-funding

In each data collection wave, we will collect semi-structured interviews from all eligible participants, web-based surveys from eligible clinicians and supervisors, and grant-related documents for review from eligible state agency administrators

*NA* not applicable (i.e., data are not collected because the data collection wave falls more than five years post-funding)

^a^ Treatment organizations that reported not sustaining the Adolescent Community Reinforcement Approach (A-CRA) in the previous wave will not be eligible unless they report having restarted A-CRA delivery since the previous wave

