##### Sustainment

We define A-CRA sustainment over the 5-year post-grant period using a 10-element measure developed in our previous research [68], which captures the ongoing quality of treatment delivery, staffing, and supervision (see Table 3). These elements are pragmatic [75] to collect from treatment organizations and center on program-level processes, rather than clinical outcomes, as recommended for sustainment measures [76].

The A-CRA sustainment elements are collected via interviews (5 from supervisors, 4 from clinicians) except for the A-CRA knowledge test for clinicians, which is collected through the web-based survey to match how the test is typically administered. Each element will be assessed as follows: (1) clinician knowledge via a 10-item multiple choice survey, (2) supervisor knowledge using a 15-item true/false questionnaire, presence of certified (3) clinicians(s) and (4) supervisor(s) is self-reported and verified with CHS records, (5) usage by the self-reported percent of eligible youth receiving A-CRA in the past six months, (6) dosage by clinicians’ self-report of the number of sessions delivered (12–14 prescribed), clinicians also report whether clinical supervision (7) occurs biweekly, (8) involves six key activities, and (9) includes a review of recorded sessions, and (10) quality of A-CRA training plans submitted by supervisors will be rated by CHS staff (i.e., percentage of expected training components included). A composite A-CRA sustainment score is created by normalizing each element (on a 0 to 1 scale, averaged across all ratings from the same treatment organization), then summing the normalized scores (i.e., composite scores range from 0 [no] to 10 [complete] sustainment) [68].

We will also measure clinicians’ and supervisors’ global ratings of A-CRA sustainment using the newly published, three-item Provider Report of Sustainment Scale [77]. This offers a point of comparison for our primary sustainment measure.

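### Copying the earlier 41/59 role mix plans 81 clinicians for 91 organizations, so about one organization in nine would have no observed source for the clinician half of the sustainment composite

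*Protocol article*

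**What the plan says.** The Treatment organizations section fixes the sampling frame ("These procedures selected 91 organizations") and describes the earlier sample, which "had an average of 2.17 participants per organization (41% clinicians, 59% supervisors"). For the new sample it adds "and we will aim for a similar breakdown of participants" and sets a ceiling: "A maximum of 197 clinician and supervisor participants may be included in the state-focused grant sample". Table 1 turns this into expected respondents by cohort; for cohort 1, for example, "7 states 37 organizations" and "33 clinicians 47 supervisors".

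The Sustainment outcome section and Table 3 give the source of each composite element. Supervisors supply five by interview. Clinicians supply four by interview (dosage, supervision frequency, supervision content, use of session review) and a fifth, clinician knowledge, by web survey. Ratings are averaged within an organization and the score is formed by "then summing the normalized scores" on a 0 to 10 scale. Tables 2 and 3 also assign the Implementation Leadership Scale, an a priori moderator in Aims 1 and 2, to clinicians only.

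The Quantitative data analysis section attributes missing data to nonresponse and to the timing of the waves, and applies multiple imputation and reweighting to the nonresponse. The article sets no minimum of one clinician per organization.

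**The concern.** The composite needs both roles from each organization, yet the recruitment aim is written as an overall ratio of roles. That ratio, at 2.17 respondents per organization, gives fewer than one clinician per organization. The shortfall therefore arises from the target and is not a consequence of people declining to take part.

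Two analyses are affected. In an organization with no clinician, half of the main sustainment measure has no observed value and would have to be modeled from the supervisor elements, other waves and other organizations. The leadership moderator has no value there either, and the Statistical power section already expects to detect only large or medium moderation effects (0.89 SD in Aim 1, 0.69 SD in Aim 2).

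**Working it through.** **Inputs.** Target organizations by cohort, Table 1: 37, 33, 21. Expected clinicians: 33, 29, 19. Expected supervisors: 47, 42, 27. Earlier sample: 169 respondents at 78 organizations, 41% clinicians.

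**Step 1: reproduce the plan's ceiling.** 169/78 = 2.17 respondents per organization. 91 × 2.17 = 197.5, against the stated 197. Table 1 agrees: 33 + 29 + 19 = 81 clinicians and 47 + 42 + 27 = 116 supervisors, total 197. The shares are 81/197 = 41.1% and 116/197 = 58.9%. Table 1 is thus the old mix applied at the ceiling.

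**Step 2: clinicians per organization.** 2.17 × 0.41 = 0.89.

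**Step 3: lower bound on organizations with no clinician.** If each clinician belongs to a different organization, the number with none is organizations minus clinicians. By cohort: 37 − 33 = 4, 33 − 29 = 4, 21 − 19 = 2. In total 91 − 81 = 10, and 10/91 = 11.0%. Every organization that supplies two clinicians adds one to this count.

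**Step 4: how the bound moves with the number of organizations.**

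| Organizations | Clinicians | Minimum with none |
|---|---|---|
| 91 | 81 | 10 |
| 85, mix scaled | 85 × 2.17 × 0.41 = 75.6 | 9.4, so about 9 to 10 |
| 85, all 81 clinicians still recruited | 81 | 4 |

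Cohort 1 lists 37 organizations in 7 states although the sampling cap of five per state allows 35. With 89 in total the bound is 89 − 81 = 8, inside the same range.

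**Step 5: share of the composite affected.** Clinician elements: 4 + 1 = 5 of 10.

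**Step 6: the comparison sample.** 0.41 × 169 = 69.3 clinicians for 78 organizations, so at least 78 − 69.3 = 8.7, about 9 (11%), had none.

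**Step 7: scale of the precision loss (illustration).** Assume the bounds are reached, organizations without a clinician contribute nothing, per-organization variance is equal in both groups, and state-level correlation is ignored. The standard error of the contrast then grows by √[(1/81 + 1/69)/(1/91 + 1/78)] = √(0.02684/0.02381) = 1.06, about 6%. Imputation would recover part of this; clustering of clinicians would enlarge it.

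**Step 8: room within the ceiling.** One clinician in each organization needs 91 clinicians, 91/197 = 46.2% of places. One of each role needs 91 + 91 = 182, leaving 15.

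**The case against.** Table 1 reports expected respondents and the mix is an aim. No clinician cap exists, 91 clinicians fit within 197 places, and people who decline one wave are invited again. This stands: the plan expects a gap but does not impose one, so a reader who inferred that the clinician elements cannot be observed would go too far. The written aim and the expected counts nevertheless both point recruiters toward the gap.

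Some supervisors may also treat clients and answer the clinician items. The article allows a person to hold both kinds of certification, and the role-tailored instruments are in additional files that are not shown. This stands as a condition on the bound.

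A reader might infer that organizations without a clinician are capped at 5 of 10 and their sustainment understated. The article does not support that: nowhere does it score an absent element as zero, and scoring with one role missing may be settled in the full plan.

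A reader might also infer bias in the grant-type contrast. Step 6 speaks against it, since the earlier sample has much the same shortfall.

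Finally, if roles fell at random within organizations with two or three respondents, about 29 of 91 would have no clinician (0.83 × 0.59² + 0.17 × 0.59³ = 0.324). The article gives no basis for random roles, and recruiters know which roles they need, so this figure should not be used as an estimate.

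**Conclusion.** The concern holds as a weakness of the recruitment target. Met as written, it leaves at least 10 of 91 state-focused organizations (11%) without a clinician, or about 4 to 10 if about 85 take part. In these, five of ten sustainment elements and the leadership score would depend on imputation that the article describes for nonresponse. This rests on Table 1's counts and on supervisors not answering clinician items.

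The demonstrated cost is lost precision, modest at the lower bound, and heavier dependence on the imputation model in both grant types. Neither a bias in the contrast nor a downward distortion of the composite is shown.

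**What to change.** Replace the aim of matching the earlier mix with a coverage priority: in each organization, recruit at least one clinician and one supervisor where both exist, then use remaining places freely. Revise Table 1's expected counts to match.

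State one scoring rule for both grant types. When a role was not interviewed, its five elements are missing. Keep this separate from organizations that no longer deliver A-CRA, where the plan's own scoring of no sustainment applies. Say that the imputation model also covers an absent role, and report element completeness by grant type.

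The ceiling of 197, the instruments and the eligibility criteria stay as they are. The old ratio has no analytic role, because elements are role-specific and averaged to the organization; the article bases pooling on consistent eligibility criteria.

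There are two costs. Full coverage depends on both roles being available and willing, so some gaps will remain. And because the earlier data are fixed, role mix and completeness will differ somewhat between grant types, which is why completeness should be reported and the scoring rule shared.
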